##### Stress

Subjective stress levels will be assessed with the Depression, Anxiety, and Stress Scale-21 Items (DASS-21), a validated and reliable measure of core symptoms associated with depression, anxiety, and stress [18]. We will also use a visual analog scale (VAS; “Please rate your current stress level”: 0=no stress, 10=extreme stress) to assess current subjective stress levels [19].

##### Craving and Demand

The Stimulant Craving Questionnaire (STCQ) will be used to assess current craving [20]. The STCQ is a 10-item inventory that is useful in measuring craving across both stimulant types (cocaine and methamphetamine). The drug purchasing task will be used to assess demand for stimulants. During the hypothetical drug purchasing task, participants indicate how much of the drug they would use based on increasing prices [21-25]. Participants will complete a version of the drug purchasing task based on their primary stimulant use disorder (cocaine or methamphetamine).

##### Safety, Side Effects, and Other

A 31-item questionnaire will be administered to participants in the suvorexant group only to assess side effects and adverse events. The Columbia Suicide Severity Rating Scale [26] will be administered at each laboratory visit, and the Beck Depression Inventory [27] will also be included in the self-report battery. Additionally, at the first in-person visit, the Addiction Severity Index will also be administered to assess substance use severity and collect relevant demographic and addiction-related information [28].

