**Methods:**

A total of 40 participants, recruited from a residential treatment facility, will be randomized (1:1) to either 7 days of nightly suvorexant (10 mg) or treatment as usual. Participants’ sleep will be monitored using an activity tracker watch, and they will complete a sleep diary each night to confirm bedtimes and wake-up times. Participants in the suvorexant group will receive the study medication for 7 nights. On premedication and postmedication study days, participants will be transported to the Center for Neurobehavioral Research on Addiction to complete the study sessions. At both study sessions, participants will complete self-report and safety measures (safety measures for the suvorexant group only) followed by administration of a stress reactivity test and an electroencephalographic assessment.

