## Methods

### Study Design

We will use an open-label, randomized 2-group design. Participants (n=40) will be randomized to receive 7 days of suvorexant (10 mg) or TAU, consisting of supportive care and symptomatic medication. Figure 1 outlines the schedule of events. Informed consent, eligibility criteria, and baseline sleep data (via actigraphy) will be assessed on day 0 of the study via telephone or video call. Day 0 will ideally occur around 4 days (but within the first week) following admission to the residential program. On day 1 and day 8, participants will be transported to the outpatient treatment research clinic at the Center for Neurobehavioral Research on Addiction (CNRA) to complete the study sessions. At each study session, participants will complete self-report and safety measures (safety measures for the suvorexant group only) followed by administration of the stress reactivity test and then the EEG assessment. Details regarding each of these procedures are provided in subsequent sections. Participants in the suvorexant group will begin receiving the study medication, administered by residential nurses, from day 1 up until day 8 (ie, nights 1‐7). All participants will remain in the residential program until either regular discharge at approximately 30 days (“successful completion”) or early departure (eg, patient-directed discharge or leaving against medical advice). This design captures the critical first 2 weeks of stimulant withdrawal, when sleep disruptions and other withdrawal-related symptoms are typically most pronounced [7].

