### Intervention

Suvorexant is a dual orexin receptor antagonist approved by the FDA for the treatment of insomnia. In this study, we will administer 10 mg of suvorexant for 7 nights. Two prior studies from our group suggested that suvorexant could be safely administered to individuals with cocaine use disorder [4] and methamphetamine use disorder [10]. The half-life is about 12 hours on average, and steady-state plasma concentrations occur in 3 days with daily administration [11]. A nurse at the residential programs will administer the medication to participants in the suvorexant group each evening before bedtime, at the same time nightly (around 10 PM), with a medication log to monitor compliance.

All participants will receive TAU, consisting of standard programming from the inpatient facilities, including a combination of individual therapy, group therapy, 12-step meetings, case management, and recreational therapy. Participants in the suvorexant group will receive suvorexant and will be asked to avoid medications listed in the exclusion criteria, including sleep-related medications. Participants in the TAU group will continue their usual medication regimen as prescribed by the inpatient facility staff. A comprehensive list of medications prescribed for each patient will be collected. If possible, statistical analyses will attempt to control for other medication exposure.

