### Ethical Considerations

The study protocol was approved by the Committee for the Protection of Human Subjects at UTHealth, Houston, Texas (HSC-MS-24‐0330). Consent will be obtained virtually at the inpatient facility by a member of the CNRA team via voice or video call. Interested participants will e-sign the consent via REDCap. A copy of the signed consent can be printed or emailed to the participant. The PI will be responsible for ensuring compliance with the policies of the local institutional review board (the UTHealth Houston Committee for the Protection of Human Subjects). All participant data will be kept confidential. Data and safety oversight will include staff training, weekly audits of data collection and entry, medical screening with results reviewed by an on-site nurse or physician, use of standardized assessments, continued medical monitoring during the study, and procedures to monitor medication compliance. A data safety monitoring board will provide additional, independent oversight of data related to participant safety. All adverse events will be recorded for duration, severity, and frequency, and an evaluation will be made as to the event’s relationship to the study drug, classified as unrelated, unlikely, possible, or probable. Participants will be compensated for their time as follows: US $5 for the screening and consent, US $40 for laboratory visits, US $10 for questionnaires, US $1 per day for medication adherence, and US $50 completion bonus.

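### Side effects are systematically prompted in the suvorexant arm only, so the trial has no concurrent control rate for the 31 questionnaire items

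*Protocol article*

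**What the plan says.** The restriction is explicit and consistent. Under Safety, Side Effects, and Other: "A 31-item questionnaire will be administered to participants in the suvorexant group only to assess side effects and adverse events". Study Design describes the day 1 and day 8 sessions and adds "safety measures for the suvorexant group only"; the Methods paragraph of the Abstract has the same limit.

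Other statements bear on the point:

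- **Timing.** Study Design says of the study window: "This design captures the critical first 2 weeks of stimulant withdrawal, when sleep disruptions and other withdrawal-related symptoms are typically most pronounced".
- **Control arm medication.** Under Intervention: "Participants in the TAU group will continue their usual medication regimen as prescribed by the inpatient facility staff". Suvorexant participants are asked to avoid the medications in the exclusion list, including those for sleep.
- **Adverse events in general.** Under Ethical Considerations: "All adverse events will be recorded for duration, severity, and frequency", with no limit to one arm, and "an evaluation will be made as to the event’s relationship to the study drug", graded on a four-level scale.
- **Columbia scale.** Under Safety, Side Effects, and Other: "The Columbia Suicide Severity Rating Scale [26] will be administered at each laboratory visit". This sentence names no arm.

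**The concern.** The trial has a randomized control group in the same residential setting that attends the same two sessions, yet this instrument is withheld from it. By the article's own account, symptoms are expected in both arms during this window. A checklist completed by one arm cannot show how many of its endorsements would have occurred without the drug.

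Two readings of the data are then available, and both are weak. The first is the change from day 1 to day 8 within the suvorexant arm, which mixes any drug effect with the natural course of withdrawal. Easing withdrawal can hide a drug effect, and persisting withdrawal can imitate one. The second compares suvorexant reports prompted item by item with whatever TAU participants mention unasked. Even with no drug effect, that comparison leans towards more events on suvorexant.

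At stake is what the trial can tell a later, larger trial about tolerability. This is a data-collection rule, so no analysis plan can repair it afterwards.

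**Working it through.** The article gives no safety rate, power or precision, so there is no stated figure to reproduce. The check sets the sections side by side and then illustrates the size. All symptom rates below are assumptions.

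**1. Is there an equivalent for TAU?** Three places restrict the questionnaire or the safety measures to suvorexant (Abstract, Study Design, Safety section), and no section gives TAU the same checklist. The adverse-event statement under Ethical Considerations may cover TAU, but it describes no systematic prompting there.

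**2. Is there a baseline?** Yes, in the suvorexant arm. Safety measures are taken at both sessions, and Intervention places dosing at about 10 PM, so the day 1 session precedes the first dose. Only the concurrent TAU course is missing.

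**3. What one arm alone can show.** Take 20 treated participants (Statistical Analysis Plan: 40 in total, 20 per arm), of whom 6 endorse an item.
- Suvorexant rate: 6/20 = 30%; exact (Clopper-Pearson) 95% interval 11.9% to 54.3%.
- Risk difference with the TAU rate uncollected: from 0.30 − 1 = −0.70 to 0.30 − 0 = +0.30.
- With 4/20 the bounds are −0.80 to +0.20; with 10/20 they are −0.50 to +0.50.

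The sign is undetermined in each case.

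**4. Prompted against unprompted.** Let both arms have the same true item rate p, and let TAU mention a fraction f of those symptoms unasked. The apparent excess on suvorexant is p(1 − f). At p = 20% it runs from 0 points (f = 1) to 20 points (f = 0). It is never negative. Its actual size is unknown because the article gives no f.

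**5. Background endorsements.** At an assumed 10% to 20% rate per item, a participant endorses 31 × 0.10 = 3.1 to 31 × 0.20 = 6.2 items with no drug effect. These would appear on day 1 as well as day 8.

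**6. Both arms asked.** The half-width of the 95% interval for the risk difference is 1.96 × √(2p(1 − p)/n).
- p = 0.20, n = 20: 1.96 × √(2 × 0.2 × 0.8/20) = 0.248, about 25 points.
- p = 0.30, n = 20: 0.284, about 28 points. With 18 per arm (the article's 10% attrition): 0.299, about 30 points.

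**7. Those still to enrol.** At submission 8 of 40 had been enrolled, leaving 32, or 16 per arm at 1:1. At p = 0.20: 1.96 × √(2 × 0.2 × 0.8/16) = 0.277, about 28 points. Current enrolment is not known.

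**8. Columbia scale.** The Safety section gives it at each laboratory visit without naming an arm, while Study Design and the Abstract limit safety measures to suvorexant. If the scale counts as a safety measure, these statements conflict.

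**The case against.** The strongest case on the other side has five parts.

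- **The control is not discarded for safety as a whole.** The sleep scales (ISI, PROMIS-SF), the stress scales (DASS-21, visual analog scale), the Beck inventory, heart rate and blood pressure carry no arm limit. For the symptoms they cover, a randomized comparison exists. This stands, and it limits the point to what only the 31 items would capture.
- **A pre-drug score exists.** A reader might infer that causality must be judged with no background information at all. The documents do not support that: each treated participant has a day 1 score taken in early abstinence. The confounding of change with withdrawal remains.
- **Adverse events are to be recorded without an arm limit.** A reader might infer that TAU events are not collected. The article does not say so, and the full protocol may describe how they are obtained. What remains is that the article describes systematic prompting for one arm only.
- **No aim compares safety between arms.** The three aims concern sleep, the secondary mechanistic outcomes, and length of stay and program completion. The checklist may be meant for individual monitoring, so calling the safety result uninterpretable would go too far.
- **The remedy is weak.** With both arms asked, power for 40% against 20% (assumed rates, two-sided 0.05) is about 28% with 20 per arm and 25% with 18. The Discussion itself acknowledges that subjective outcomes in an open-label trial are vulnerable to expectancy, and TAU participants take other medication. The new contrast would therefore not be unbiased. This stands, but the trial's declared purpose is to estimate plausible ranges for later trials, and a wide estimate serves that purpose better than none.

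**Conclusion.** The point holds in a limited form. The stated rule prompts side effects systematically in one arm, leaves the treated arm's change confounded with withdrawal, and tilts any comparison with unprompted TAU reports towards more events on suvorexant. At 6 of 20 endorsing an item, the questionnaire leaves the risk difference anywhere from −70 to +30 points. Asking both arms would replace that with an estimate carrying a half-width of about 25 points at an assumed 20% item rate with 20 per arm.

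The item rates are assumptions and the 31 items are not shown, so the size for any particular symptom is unknown. The consequence is confined to tolerability. Neither the efficacy outcomes nor the effect sizes quoted in the design analysis (Cohen d of 0.26 and 0.39) depend on it. The change is worth making because it is cheap and cannot be made retrospectively.

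**What to change.** 1. Give the same 31-item questionnaire to both arms at the existing day 1 (pre-dose) and day 8 sessions, and tabulate new or worsened items by arm.
2. Base the between-arm table on participants randomized after the change, and report earlier suvorexant questionnaires separately.
3. Label the contrast as suvorexant against TAU including TAU's own medication, reported by participants who know their allocation, with intervals and no claim of a definitive safety comparison.
4. Reconcile the Abstract and Study Design with the Safety section on whether TAU receives the Columbia scale.

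**Cost.** A few extra minutes for TAU participants at two sessions they already attend. TAU participants enrolled before the change will lack these data, which should be reported. At the submission count of 8 enrolled, most of the trial could still contribute. The contrast will remain imprecise and open to expectancy bias.

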### Laboratory Assessments

#### Sleep

Resting-state EEG will be collected on laboratory days to assess the waking effects of sleep quality. The outcome variable will be alpha power (8‐12 Hz), which reflects a state of wakeful rest [5,29]. Both eyes open and eyes closed conditions will be measured and analyzed separately. Resting alpha power will be collected at each laboratory visit day. Refer to the EEG Protocol section for details.

#### Stress

The socially evaluated cold pressor test will be used to measure stress reactivity. This task reliably activates the sympathetic nervous system and the hypothalamic-pituitary-adrenal (HPA) axis, as evidenced by increases in heart rate (HR), blood pressure (BP), and cortisol levels [30-33]. The social evaluative component is used to enhance HPA-axis activation. Participants will face a computer monitor showing their face using a webcam and a confederate wearing a white laboratory coat and clipboard will also be in the room. Participants will be informed that the camera is recording their facial reactions for later analysis and that the physician in the white laboratory coat will also be taking notes on their stress responses. No facial recordings or actual notes will be taken. During the cold pressor test (CPT), participants will submerge their arm in an ice-water bath. Physiological measures of stress reactivity will include HR, BP, and salivary cortisol, consistent with previous studies from our group [19,34]. Saliva samples will be collected before and after the CPT using the Cortisol-Salivette system (Sarstedt) and analyzed with the Cortisol ELISA Kit (Enzo Life Sciences), per manufacturer instructions. Subjective stress will be assessed before and after the CPT using a single-item VAS question, and HR and BP will also be recorded before, during, and after the CPT.

#### Reward Processing

EEG will also be recorded during the doors task to elicit the RewP [6]. In this task, participants are shown 2 doors, one of which has a hypothetical prize behind it. Participants guess which door hides the prize and then receive feedback indicating the outcome (up arrow=monetary win, down arrow=monetary loss). The RewP will be quantified as the mean amplitude in response to monetary feedback. Refer to the EEG Protocol section for details.

### EEG Protocol

On laboratory days, participants will be seated comfortably in front of a monitor, fitted with the EEG cap, and the electrodes will be prepared with conductive gel. EEG will be collected using a 64-channel actiCAP electrode cap, amplified with BrainAmp MR (Brain Products GmbH) and digitized using BrainVision Recorder (Brain Products GmbH). The sampling rate will be 250 Hz, and data will be filtered with a 0.1 Hz high-pass filter and a 100 Hz low-pass filter.

Resting-state EEG will be collected prior to the doors task. We will collect resting-state EEG for 3 minutes with eyes open and eyes closed.

EEG data reduction will be performed with Brain Vision Analyzer 2 (Brain Products GmbH), MATLAB (MathWorks), and BESA (BESA GmbH). Resting-state data will be analyzed using the fast Fourier transform. The outcome of interest will be alpha power (8‐12 Hz). The doors task data will be segmented (from 200 ms prestimulus to 800 ms poststimulus) by the following conditions: wins and losses. The RewP will be defined as the mean poststimulus amplitude over the frontal electrodes.

### Dissemination Plan

The PI will be responsible for keeping the study record up to date on a yearly basis and for posting the results of the clinical trial on ClinicalTrials.gov. Findings will also be disseminated through conference presentations and publications in peer-reviewed scientific journals.

### Statistical Analysis Plan

Analyses will be conducted within a generalized linear mixed modeling framework, which provides the flexibility to accommodate non-Gaussian outcomes via link functions and repeated or multilevel measurements via random effects. Traditional methods (eg, both 1-tailed and 2-tailed *t* tests and ANOVA) are subsumed as special cases, and the framework supports further extensions for nonlinear effects, time-varying predictors, and multivariate outcomes. For aims 1 (sleep) and 2 (all secondary measures), analyses will model each outcome variable as a function of the time and treatment interaction, controlling for main effects (fixed effects: outcome=β_0_ + β_1_ × treatment *+* β_2_ × time *+* β_3_ × treatment × time), with random effects to handle correlated observations. For aim 3 (treatment completion), analyses will model each outcome as a function of treatment.

All models will use distribution families and link functions as appropriate for each outcome (eg, dichotomous outcomes: binomial, with logit link). Longitudinal models evaluating change via interaction terms (eg, treatment × time) will be reduced to main effects if change is unsupported, and both models will be reported. Model fit information criteria (Akaike information criterion; leave-one-out information criterion) will be used to select structural components including multilevel (eg, random intercepts and slopes) and nonlinear terms. Analyses will be performed in R [35] via packages lme4 [36], rstan [37], and brms [38]. Potential confounders will be identified empirically [39,40] (ie, associated with both predictor and outcome) and modeled with and without adjustment; models with unchanged inference will favor parsimony. Sample characteristics (eg, sex, age, and education) will be evaluated as potential confounders. Analyses will be run in parallel using frequentist and Bayesian models. Frequentist results yield the probability of the data (or data more extreme) given the null hypothesis, whereas Bayesian results directly yield the probability of an alternative hypothesis [41,42]. Frequentist models will use *α*=.05 with false discovery rate correction for exploratory tests. Bayesian priors will be weakly informative (β*~* N(0,1); sd~ Half-Cauchy(0,1); correlation matrices ~ LKJ(2)). Bayesian models will be evaluated via posterior probability (PP) threshold guidelines in the literature [43,44], suggesting that PP=75% to 90% indicates moderate evidence, PP=91% to 96% indicates strong evidence, and PP=97% or above indicates very strong to extreme evidence. Posterior predictive checking, scale reduction factors (“rhat”), and effective sample size will be used to evaluate Bayesian assumptions. Evaluation for frequentist models will use graphical evidence and statistical tests. Generalized linear mixed models inherently accommodate outcome values missing at random; other missing values will be handled by imputation or pattern-mixture modeling. Analyses will follow intention-to-treat principles.

The current proof-of-concept study is designed primarily to estimate a plausible range of treatment effects rather than to provide definitive hypothesis tests. To characterize expected inferential performance at the proposed sample size (n=40; 20 per arm), Monte Carlo simulation–based design analyses were conducted (1000 iterations). Data were generated under a linear mixed model with a treatment × time interaction, AR(1) correlated repeated measures (ρ=0.50), and the weakly informative priors specified earlier. At this sample size, assuming 10% attrition (n=36), simulations demonstrate at least an 80% probability (analogous to statistical power) of achieving moderate evidence (PP ≥75%) for standardized average treatment effects, unfolding in linear fashion over time, as small as Cohen *d*=0.26, and 80% probability of strong evidence (PP ≥91%) at Cohen *d*=0.39. Wide credible intervals are anticipated at this sample size, and results will be interpreted accordingly as preliminary effect size estimates to inform future definitive trials.

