### Conclusions and Future Directions

Notably, this trial was designed as a proof-of-concept study primarily concerned with deriving a preliminary range of plausible effect sizes for mechanistic effects and the effect on treatment completion. The study sample size was selected based on available funding and time to complete the study tasks. Therefore, the results of this study are meant to guide future fully powered trials rather than provide accurate efficacy estimates. A further limitation of this study is the lack of a placebo control and the open-label design. This design introduces potential biases into subjective measures due to participants’ knowledge that they are receiving the treatment. As replication in a larger controlled trial is still needed, a negative finding would not rule out efficacy. Positive findings will also need to be confirmed in a larger sample. A TAU control condition was selected as the next best option and will provide information regarding how add-on suvorexant compares to supportive care and symptomatic medication alone. Critically, the use of several objective measures of main outcomes (actigraphy, HR, BP, cortisol, and EEG) will partially offset the influence of the open-label medication. This translational research approach will be the first mechanism-focused clinical investigation of suvorexant for the treatment of StimUD. FDA approval of suvorexant for the treatment of primary insomnia helps pave the way for rapidly advancing the repurposing of orexin-based therapies for drug addiction treatment.

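### Choosing covariates by observed association with randomized arm, then favouring the unadjusted model when inference is unchanged, suits an estimation trial poorly; it matters for aim 3, reduced models and covariate × time terms

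*Protocol article*

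**What the plan says.** The Statistical Analysis Plan section of the protocol article sets a two-step rule.

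- **Selection.** "Potential confounders will be identified empirically [39,40] (ie, associated with both predictor and outcome"). The candidates are given by example: "Sample characteristics (eg, sex, age, and education) will be evaluated as potential confounders". No cut-off for association is stated.
- **Retention.** Covariates that pass are "modeled with and without adjustment; models with unchanged inference will favor parsimony". Inference is not defined here. The only inferential criteria in the section are the significance level ("Frequentist models will use *α*=.05 with false discovery rate correction for exploratory tests") and the posterior probability (PP) bands for moderate, strong and very strong evidence. No change-in-estimate criterion is given.

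The core model for aims 1 and 2 has no baseline covariate: "analyses will model each outcome variable as a function of the time and treatment interaction, controlling for main effects". Aim 3 outcomes are modelled on treatment alone. Interaction models in which change is unsupported are reduced to main effects.

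The same section says the study is "designed primarily to estimate a plausible range of treatment effects rather than to provide definitive hypothesis tests". Conclusions and Future Directions repeats that it is "primarily concerned with deriving a preliminary range of plausible effect sizes for mechanistic effects and the effect on treatment completion".

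**The concern.** Both steps read a null result as if it showed that the covariate does not matter.

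In the first step, allocation is randomized, so an association between arm and a pre-randomization characteristic reflects chance. Testing for it says little about whether adjustment is worthwhile. What matters is how strongly the characteristic predicts the outcome, and that can be judged in advance. A prognostic covariate that happens to look balanced is never used.

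In the second step, a covariate that has passed the screen still yields to the unadjusted model if the inference is the same both ways. With 36 to 40 participants the verdict will often be the same even when the estimate has moved substantially. If inference is read through the stated criteria, the favoured model is chosen by verdict, while what the trial passes to its successor is an estimate and its interval.

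**Working it through.** **Inputs from the protocol article.** 40 participants, 20 per arm; 36 after 10% attrition, so 18 per arm; alpha .05; AR(1) correlation 0.50; design effects d=0.26 (PP at least 75%) and d=0.39 (PP at least 91%), each with 80% probability.

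**Assumptions, because the article gives none.** One continuous baseline covariate with outcome correlation r=0.3 or 0.5; screen at two-sided p<.05; inference unchanged means the same side of .05; one post-treatment comparison on a continuous outcome.

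**1. The plan's own figure, for scale.** Take two time points and a linear effect averaging d, so 2d at the end.
- The standard error of treatment × time is √(2 × 2(1 − 0.5)/18) = 0.333.
- Under the N(0,1) prior, PP reaches c when the estimate exceeds z(c) × 0.333 × √(1 + 0.333²).
- d=0.26: the cut is 0.237, and Φ((0.52 − 0.237)/0.333) = 0.80.
- d=0.39: the cut is 0.471, and Φ((0.78 − 0.471)/0.333) = 0.82.

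The stated 80% is thus reproduced closely. It does not depend on the covariate rule.

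**2. The screen.**
- The standard error of a chance imbalance is √(2/18) = 0.333 SD. An imbalance of at least 0.5 SD has z = 0.5/0.333 = 1.5 and arises in 13% of trials per covariate.
- The noncentral t distribution gives power 0.308 to flag a true 0.5-SD difference at 18 per arm, so 69% are missed. At 20 per arm power is 0.338, so 66% are missed.

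**3. Cost over all trials.** The closed form for the root mean squared error (RMSE) of a fixed adjusted estimate is √(2/18) × √(1 − r²) × √(1 + 1/32), the last factor being the price of estimating one slope.

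| r | Never adjust | Rule (simulated) | Fixed adjustment (closed form) |
|---|---|---|---|
| 0.3 | 0.333 | 0.33 | 0.32 |
| 0.5 | 0.333 | 0.331 | 0.293 |

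Simulated fixed adjustment gives the same values. The rule performs almost as if nothing were ever adjusted, because a covariate passes the double screen in only about 2–4% of trials. Most of the lost precision therefore comes from the screen.

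**4. What happens once a covariate is flagged.** At n=36, r=0.5, d=0.39:
- flagged in 4.2% of trials;
- verdict unchanged in 66% of those, so the unadjusted model is favoured;
- in those trials the two estimates differ by 0.39 SD on average, and RMSE is 0.53 unadjusted against 0.33 adjusted.

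At r=0.3 the corresponding shift is 0.32–0.33 SD and RMSE is 0.46 against 0.36.

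**5. Sensitivity to the undefined terms.** Over a wider grid (r=0.3 to 0.7, n=36 or 40), a p<.20 screen flags 13–20% of trials. Once flagged, the verdict is unchanged in 53–93% of cases if inference means p<.05, and in 27–69% if it means the PP band.

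**6. Error rate and power.** With no effect, rejection under the rule is 0.044–0.048. At d=0.8, power is 65% against 76% for fixed adjustment (r=0.5), or 64% against 67% (r=0.3).

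**7. Which models are affected.** With two complete visits, the treatment × time estimate is the difference between arms in mean change. A covariate entered as a main effect adds the same amount at both visits and cancels. In a simulated two-visit data set:

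| Model | Treatment × time | Treatment main effect |
|---|---|---|
| No covariate | 0.385 | 0.705 |
| Covariate, main effect only | 0.385 | 0.134 |
| Covariate × time added | 0.008 | 0.322 |

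With 10% random dropout at the second visit, the main-effect covariate moved the interaction by only 0.01–0.02 SD. The figures in steps 3, 4 and 6 therefore do not describe the aim 1 and 2 interaction as written.

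**The case against.** The strongest objection is that the magnitudes belong to a model the trial does not use for its main aims. For the linear treatment × time contrast this is correct, and it limits the point. A reader might infer that the main sleep result could be off by about 0.4 SD. The documents do not support that, because stable differences between participants already cancel in the change.

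A reader might also infer that the favoured estimate is confounded, or that false positives rise. Neither holds. Randomization makes the unadjusted estimate unbiased on average, and the rejection rate under no effect is slightly below .05. What remains is error conditional on a chance imbalance.

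Three further objections stand in part.

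- **The threshold is a reading of the text.** Unchanged inference is undefined and could be meant to include the estimate and its interval. But alpha and the PP bands are the only criteria stated.
- **Both models are fitted, and the rule favours rather than discards.** That softens the harm. However, the section's explicit promise to report both models concerns interaction versus main-effects models, not adjusted versus unadjusted ones.
- **Covariate lists are often left to a fuller plan.** True, and the absence of a list is not the point. The article states a selection rule, and it is the rule that is poorly chosen.

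Finally, r=0.5 may be generous for sex, age or education. At r=0.3 the overall gain from fixed adjustment is about 0.01 SD in RMSE.

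**Conclusion.** The point holds within limits. The rule screens covariates on an association that randomization makes a matter of chance, and it ranks models without reference to the size of the change in the estimate. That fits poorly with a trial whose declared product is a range of effect sizes.

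It affects aim 3, longitudinal models reduced to main effects, and any model using covariate × time. It does not affect the linear treatment × time coefficient when covariates enter only as main effects and data are complete.

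The average loss is modest: RMSE of 0.33 against 0.29 at r=0.5, and 0.33 against 0.32 at r=0.3. The larger errors arise only in the roughly 2–4% of trials per covariate in which the p<.05 screen is passed. The power gap is quoted at d=0.8, about twice the larger design effect, and should be read with that in mind.

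The figures rest on the assumed screen, a single continuous covariate and a continuous outcome. They are a guide to length of stay, and do not carry over directly to a logistic model of program completion.

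**What to change.** Delete the empirical screen and the parsimony clause from the Statistical Analysis Plan, and state instead:

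> The main model for each outcome adjusts for a short fixed set of pre-randomization characteristics chosen for expected prognostic value (for example age, sex and primary stimulant), regardless of observed balance or statistical significance. In treatment × time models, these enter with a covariate × time term where they are intended to affect that contrast. The unadjusted estimate is reported alongside. The difference between the two estimates and their intervals, not a change of verdict, describes sensitivity to adjustment.

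The covariate × time sentence is needed: without it the adjustment would do nothing for the aim 1 and 2 interaction. The Intervention section's separate plan ("If possible, statistical analyses will attempt to control for other medication exposure") concerns exposure after randomization, so it does not belong in this set. For completion, the adjusted and unadjusted odds ratios can differ even under perfect balance, so the comparison should be read with that in mind.

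**Cost.** Wording only: the variables are already collected and both models are already planned. The article reports 8 of 40 participants enrolled and no outcome data available at submission. The statistical price is a few degrees of freedom. For k unrelated covariates in a linear comparison, the variance rises by a factor of about 1 + k/(N − k − 3). With N=36 and k=3 this is 1 + 3/30 = 1.10, or about 5% on the standard error. Three covariates break even once they jointly explain about 9% of the outcome variance (1 − 1/1.10), which is why the list should stay short.
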